## Abstract

**Background/Objectives**: Neck pain is a complex biopsychosocial condition that affects a significant proportion of the global population. Projections indicate that over the next 30 years, cervical pain will impact approximately 269 million individuals, positioning it as one of the primary drivers of healthcare expenditure and system burden worldwide. While exercise is a key approach for neck pain, the effectiveness and cost-effectiveness of treatments delivered remotely remain underexplored. The aim of this study is to analyse the cost-effectiveness and cost-utility of the treatment of non-specific neck pain through a telerehabilitation programme based on cervical exercise and analgesic electrotherapy. **Methods**: This is a study protocol for an economic evaluation based on a randomised controlled trial (RCT) with a sample size of 210 participants (*N* = 210). The sample will be evenly divided into two groups to perform the same cervical exercise programme combined with electroanalgesia: one group will receive the intervention via telerehabilitation, and the other will receive the intervention face-to-face. Three sessions will be held per week for eight weeks for a total of 24 sessions. Demographic and clinical data of the participants, healthcare resource utilisation, and associated costs will be collected. Assessments will be carried out throughout the study: before the first session (baseline), at 8 weeks (post-intervention), and 6 months after completion of the treatment (follow-up). **Discussion**: This study will make a significant contribution to reducing costs and improving the treatment of patients with non-specific chronic neck pain. The social perspective associated with economic evaluation will enable the investigation of indirect costs such as work absenteeism or expenses borne by the patient, providing useful data to optimise planning and decision-making in the healthcare sector.

## 1. Introduction

Neck pain (NP) is a complex biopsychosocial condition associated with a reduction in quality of life, decreased work productivity, limitation of activities of daily living, and increased use of healthcare services [1]. It is estimated to affect between 20 and 70% of the adult population over the course of their lives [2]. The prevalence of NP is indeed high worldwide, mainly affecting the working-age population (peaking between 45 and 74 years) and impacting women to a greater extent both in terms of prevalence and years lived with disability [3,4]. While acute NP usually resolves within two months, approximately 50% of individuals report persistent pain after one year [5], and up to 60% of the working population experience a recurrence in the year following their initial episode [6]. If the duration of symptoms persists for 12 weeks or more [7], it acquires the status of chronic pain, and if pathognomonic signs and symptoms have also been ruled out, it may be classified as non-specific pain [8]. The combination of both gives rise to non-specific chronic neck pain (NSCNP), a common condition that has a significant socioeconomic impact [8]. The Global Burden of Disease 2021 analysis ranked NP 11th out of 369 causes of years lived with disability, affecting 203 million people worldwide in 2020, including 27.66 million in Europe [4]. By 2050, the global prevalence is expected to rise by 32.5%, potentially affecting 109 million (CI: 88.8–131) men and 160 million (CI: 131–192) women [4].

NP is linked to impaired work performance and imposes a considerable economic burden on both individuals and healthcare systems. In the United States, it is estimated that there are approximately 10.2 million annual visits to physiotherapists or hospitals due to NP [1]. In Belgium, Gorasso et al. estimated the direct annual cost per patient at EUR 2212—36% higher than for individuals without NP [9]. Meanwhile, the Netherlands reported total costs of USD 686 million for related conditions [10]. Economic evaluations in healthcare distinguish between direct costs (related to the use of services and resources) and indirect costs (related to lost productivity, quality of life, and reduced independence). Indirect costs often exceed direct medical and pharmaceutical expenses [11]. The majority of health-related expenditure is caused by so-called presenteeism, which refers to reduced productivity due to attending work while ill and performing below usual standards, and is simultaneously the greatest risk factor for experiencing periods of sickness absence [12]. Economic losses resulting from presenteeism due to NP constitute a global problem affecting the world’s leading economies, with annual per capita losses of USD 1290 in the USA (an approximate total of USD 11.87 billion) and USD 414.05 per capita in Japan (an approximate total of USD 28 billion) [12,13]. A key factor in reducing the costs of NP treatment appears to be early intervention, as a delayed start to treatment may result in an increase in total costs of up to 117% [14]. To truly understand the economic impact of a disease, two main types of analysis can be used: cost-effectiveness and cost-utility. In the field of health economic evaluation, cost-effectiveness analysis allows decision-making and comparison of interventions by considering both the costs of a treatment and how effective that treatment is for at least two competing strategies [15], while cost-utility analysis also incorporates quality of life [16].

There is a consensus among the highest-quality European clinical guidelines regarding the recommendation of therapeutic exercise as an essential component in the treatment of chronic neck pain (CNP), both as a standalone intervention and as part of multimodal programmes alongside education, manual therapy, or psychological approaches [17]. Recent studies have identified exercise-based therapy as a cost-effective intervention for CNP [3]. Moreover, exercise has been shown to produce immediate analgesic effects, reflected in an increased pain threshold and modulation of nociceptive sensitivity [18]. In individuals with NSCNP, both isometric and joint mobility exercises have demonstrated hypoalgesic effects—not only at the site of pain but also in distant body regions [19]. The McKenzie method is a widely used strategy in the management of NP that has demonstrated its effectiveness in adult patients with moderate to severe pain [20]. It is based on a comprehensive assessment that integrates medical history, physical examination, and the patient’s response to repeated movements [21]. It also addresses cognitive–sensory dimensions of pain, such as fear-avoidance and negative expectations, and promotes self-management through the performance of specific, repetitive movements that reach maximum joint range, correcting dysfunctional motor patterns and reducing functional limitations [20,21,22,23].

Since its development in 1967 [24], transcutaneous electrical nerve stimulation (TENS) has remained one of the most widely adopted choices for the treatment of musculoskeletal pain [25,26]. TENS devices are portable and affordable, allowing low-intensity pulsed electrical currents to be applied via electrodes placed directly on the skin, stimulating peripheral nerves to produce a hypoalgesic effect [27]. The frequency, intensity, and pulse duration parameters can be individually adjusted to suit clinical needs [27]. Evidence suggests supporting the use of TENS (60–100 Hz) in NP [28,29]; especially when used in conjunction with other therapies, TENS may enhance tolerance to cervical exercises, facilitate mobility, and improve stretching capacity [30].

Self-management is a critical component in the treatment of chronic musculoskeletal pain, understood as the patient’s ability to actively manage their condition on a daily basis throughout the course of the condition [31]. This process involves interrelated tasks such as the medical management of pain, adaptation to affected social roles, and emotional grieving, all mediated by psychological functions that enable the individual to monitor their behaviour, set motivating short-term goals, and adapt to their context [31]. Current evidence suggests that musculoskeletal conditions such as CNP can be effectively managed in primary care through patient-centred approaches [32]. Recent clinical practice guidelines recommend, as a first-line therapeutic approach, the combination of education, exercise, and individualised counselling, with the aim of improving understanding of the condition, promoting autonomy in self-care, and reducing dependence on the healthcare system [32,33]. It is necessary to tailor the information to the characteristics and needs of each patient, addressing, in addition to the prognosis and clinical aspects, the psychosocial and functional variables that support active and sustained recovery [33]. Recently, innovative and promising treatment alternatives have emerged through new technologies, mobile devices, and telecommunications, enabling patients to participate more actively in their treatment, promoting self-care, correlating with improvements in pain, and making treatments via E-health a promising option in the management of chronic pain [34]. Telerehabilitation is a form of telemedicine that enables the assessment, treatment, and follow-up of rehabilitation programmes at a distance for patients with various conditions, with the added potential to reduce the costs associated with healthcare provision [35]. Although still a developing field, telerehabilitation for NSCNP has shown comparable—and in some cases superior—effectiveness to conventional face-to-face programmes, particularly regarding pain reduction and disability improvement [36,37,38]. Notably, no adverse outcomes have been reported in comparison with face-to-face treatment [36,37,38].

This study aims to analyse the cost-effectiveness and cost-utility of a self-administered telerehabilitation programme based on McKenzie cervical exercises and electroanalgesia compared with the same programme delivered face-to-face in patients with NSCNP. The main objectives are to (1) determine the average cost per patient associated with each intervention; and (2) calculate and report the incremental costs and benefits associated with the implementation of the intervention via telerehabilitation in comparison with the face-to-face intervention.

## 2. Materials and Methods

### 2.1. Study Design and Ethical Approval

This study protocol will be an economic evaluation, comprising a cost-effectiveness (CEA) and cost-utility analysis (CUA), conducted alongside a multicentre, double-blind, randomised clinical trial with two intervention arms. This study will analyse the cost-effectiveness and cost-utility of a telerehabilitation programme (McKenzie exercises combined with electroanalgesia) in patients aged 30–65 years old with NSCNP compared with a control group receiving the same face-to-face programme. Participants will be randomly assigned to one of the two groups (telerehabilitation or face-to-face) in a 1:1 ratio. This protocol has been developed in accordance with the recommendations for interventional trials guidelines (SPIRIT). This study will be conducted in collaboration with the Andalusian Health Service and the Department of Nursing, Physiotherapy, and Medicine at the University of Almeria. Ethical approval was obtained from the Andalusian Biomedical Research Ethics Coordinating Committee (SICEIA-2024-000820-F3) in September 2024.

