### 2.3. Randomisation and Blinding

The selected sample (*N* = 210) will be randomly divided into two groups: one group will receive treatment through a telerehabilitation programme based on the exercise protocols of the McKenzie method combined with analgesic electrotherapy, while the control group will follow the same face-to-face programme. This allocation will be performed in an equitable and blinded manner using a list of random numbers generated by Epidat 4.2 software. These cards with individual numbers will be folded and placed in opaque envelopes so that a blinded member of the study can subsequently open the envelope and assign the subject to one of the intervention groups. Each group (telerehabilitation and control) will be divided into three subgroups according to the McKenzie classification: postural, dysfunction, and derangement. The evaluator and the statistician of the study will remain blinded throughout the entire study. The assessor will not attempt to identify the participants’ group assignments, and the data provided to the statistician will be anonymised to ensure confidentiality and unbiased analysis. To ensure anonymisation, any identifiable personal information will be deleted, and a unique ID will be assigned by the principal investigator to each participant before the data are sent to the statistician. The file containing the non-encrypted information will be kept by the principal researcher. Due to the nature of the interventions, neither the participants nor the principal researcher responsible for the treatment will be blinded.

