## 3. Ethics and Dissemination

All participants will receive detailed information, both verbal and written, about the study before giving their consent to participate. They will be told that they have the freedom to leave the study at any time without consequences. Those who agree to participate must sign two copies of the informed consent form: one will be retained by the research and evaluation team, and the other will be for the participant’s personal records. All physical documents will remain under strict confidentiality in a locked filing cabinet in the research group’s office, while electronic data will be stored in a password-protected database. The research team will ensure the confidentiality and integrity of all information collected in the study.

Participant data, group allocations, treatment records, and sociodemographic information will be encoded. In addition, the results of the questionnaires will be assessed and scored. The assessor will be responsible for securely storing the collected information, using a locked cabinet for physical documents and a password-protected computer for digital files, restricting access solely to the designated assessor.

Once the first participant has been registered, the inclusion criteria, outcome measures, and analyses will not be modified. Any changes to the protocol, including possible adjustments to the inclusion criteria, outcomes, or analyses, will be communicated to the pertinent Research Committee and will be notified in publications and presentations.

The results of the study, including those related to feasibility, will be published in a peer-reviewed scientific journal. The presentation of the results will be conducted in group format, and the confidentiality of individual data will be preserved in all public communications.

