## Figures and Tables

**Table 1 healthcare-13-03076-t001:** Cost measures.

Costs	Breakdown	Source of Cost/Unit	Cost Calculation
Direct Medical Costs			
Primary care	General medicine	Andalusian Health Service	No. of visits × rate per visit
	Nursing		
	Physiotherapy		
Emergency hospital visits	General medicine	Andalusian Health Service	No. of visits × value per visit
	Nursing		
Referrals to services	Traumatology, Rehabilitation, etc.	Andalusian Health Service	Specialty × fee per visit
Home assistance	Ambulance	Andalusian Health Service	Service × fee-for-service
	General medicine		
	Nursing		
Diagnostic tests	X-rays, MRI, CAT Scans, etc.	Andalusian Health Service	Test × test price
Medicines	Muscle relaxants, analgesics, NSAIDs, etc.	Standard drug prices according to the Official General Council of Pharmacists	Medicine × price of the medicine
Non-medical direct costs			
Patient’s transport expenses	Bus	Patient	Number of times × price each time
	Taxi		
	Own transport (petrol)		
Indirect costs			
Absenteeism	Sick leave days	Patient and according to the assigned professional classification (National Statistics Institute of Spain)	Days of sick leave × daily wage

Magnetic resonance imaging (MRI), computed axial tomography (CAT), non-steroidal anti-inflammatory drugs (NSAIDs).

**Table 2 healthcare-13-03076-t002:** Timepoints of assessments.

Timepoint	Study Moment										
	Enrolment	Treatment								Follow-up	
	0W	1W	2W	3W	4W	5W	6W	7W	8W	2M	6M
	July 2025	July–September 2025								September 2025	January 2026
Screening and enrolment											
Eligibility screening	X										
Informed consent	X										
Allocation	X										
McKenzie classification	X										
Interventions											
Telerehabilitation programme (experimental)		3 Times per week									
Face-to-face programme (control)		3 Times per week									
Assessments											
Demographic variables		X									
Economic evaluation		X								X	X

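### The trial is labelled double-blind although participants and the treating researcher are unblinded, and Table 2 puts the baseline economic assessment after allocation

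*Protocol article*

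**What the plan says.** **Label.** Section 2.1 (Study Design and Ethical Approval) calls this an evaluation "conducted alongside a multicentre, double-blind, randomised clinical trial with two intervention arms".

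**Who is blinded.** Section 2.3 (Randomisation and Blinding) states: "The evaluator and the statistician of the study will remain blinded throughout the entire study". It then adds: "Due to the nature of the interventions, neither the participants nor the principal researcher responsible for the treatment will be blinded". The same section has envelopes used so that "a blinded member of the study can subsequently open the envelope and assign the subject" to a group, and leaves the unencrypted file with the principal researcher.

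**Who reports the outcome.** Section 2.6 (Outcomes) makes healthcare resource use and its cost the main outcome. It is taken from questionnaires that participants fill in at baseline, after treatment and at six months, and is supported by a receipt log.

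**When baseline is taken.** The abstract and section 2.5 place baseline ahead of the first session or the start of treatment. Neither says that it precedes allocation. Table 2 marks allocation and "McKenzie classification" at 0W, and demographic variables and the first economic evaluation at 1W.

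**Who stores the data.** Section 3 (Ethics and Dissemination) says: "Participant data, group allocations, treatment records, and sociodemographic information will be encoded". Two sentences later the assessor is made responsible for storing what has been collected, "restricting access solely to the designated assessor".

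**The concern.** Most readers take double-blind to include the participants. Here the participants know their arm and also supply the main outcome, by recalling visits, tests, medicines, travel and sick leave. A participant who knows which programme they received may recall or attribute this use differently. Blinding the assessor does not remove that risk when the assessor receives answers rather than making the measurement. A reader who relies on section 2.1 would credit the trial with a safeguard it does not have.

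The order of allocation and baseline matters for a separate reason. Baseline utility is the first point of the QALY curve in section 2.8, and the imputation model there contains every variable of both economic analyses. If baseline is answered after the arm is known, its reporting can differ between arms, and that difference passes into the comparison.

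Assessor blinding is one of the two protections that section 2.3 does claim. A storage rule that may put allocations and treatment records in the assessor's hands leaves it unclear how that protection is kept.

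**Working it through.** The label, custody and visit order are checked by comparing sections; the article gives no figure to reproduce.

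**1. Label against roles.**

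| Role | Status in section 2.3 |
|---|---|
| Participant | not blinded |
| Principal researcher responsible for treatment | not blinded |
| Evaluator | blinded |
| Statistician | blinded |

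The label fits only if double means evaluator plus statistician. Section 2.1 does not define it that way.

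**2. Consequence for the main outcome.** Section 2.6 makes the participant the source of resource-use data, and Table 1 lists the patient as a source for transport and sick leave. With neither arm blinded, the number of unblinded reporters is 210 of 210. This is the reach of the problem and not a measure of bias.

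**3. Table 2, cell by cell.** The columns run 0W, 1W to 8W, 2M, 6M, which is 11 in all.

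- Allocation: mark in column 1 (0W).
- Demographic variables: column 1 empty, mark in column 2 (1W).
- Economic evaluation: column 1 empty, marks in columns 2 (1W), 10 (2M) and 11 (6M).

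The later economic marks fall under the follow-up columns that match the planned post-treatment and six-month visits, so the columns do not appear to have shifted in extraction. The 1W column is the first treatment week. Sections 2.4 and 2.5 still require the assessment to come before the first session, so the combined reading is: allocation, then baseline, then session one.

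**4. How baseline enters the QALY.** Section 2.8 uses the area under the utility curve. I assume straight-line segments and utility recorded at baseline (u0), 8 weeks (u1) and the last visit (u2). The first segment is then

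(u0 + u1)/2 × 8/52 years,

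so u0 has weight 4/52 = 0.077. A between-arm difference d in reported baseline utility shifts the unadjusted incremental QALY by 0.077 × d. The article gives no value of d. Baseline values may also act through the imputation model; that effect cannot be computed from the article.

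**5. Custody.** Section 3 lists allocations and treatment records as information to be encoded, then gives the assessor sole access to the collected information without excluding either. Treatment records could show the arm even if the allocation is coded: section 2.4 has telerehabilitation sessions confirmed by ID entry on the website, while face-to-face sessions are given by therapists at the services. Section 2.3, however, leaves the unencrypted file with the principal researcher, and section 3 does not say whether the assessor can read the code.

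**The case against.** The strongest reply is that the article hides nothing: the section devoted to blinding says plainly who is and is not blinded, so the error in section 2.1 is one word. This stands as mitigation. It does not make the word right, and the design statement is where readers look first. The receipt log also gives some check on recall, though participants remain the source.

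Four stronger readings are tempting, and the documents do not support them.

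- *Assessor blinding is undone.* The records are encoded, the principal researcher keeps the unencrypted file, and web session confirmations go to the responsible clinician. A sentence about scoring questionnaires stands between the two custody statements, so the collected information may mean only the questionnaires. Unblinding is possible but not shown.
- *A blinded envelope opener is a contradiction.* Blinded may mean unaware of the sequence until opening, which is allocation concealment. Nothing says that the opener is the assessor, and nothing rules it out.
- *The baseline data cannot be used for adjustment or imputation.* Baseline resource use is recall of the preceding months, which allocation cannot change; only its reporting could be affected. The article does not say when participants learn their arm. The text and Table 2 do not contradict each other either, since both permit baseline after allocation and before treatment.
- *Every outcome is participant-reported.* This is documented for resource use. The Neck Disability Index appears only in the sample-size section and the abbreviations, with no mode of administration, and no utility instrument is named.

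**Conclusion.** The point holds in three parts of unequal strength.

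- **Certain:** the double-blind label contradicts section 2.3, and it matters because all 210 participants report the main outcome without blinding.
- **Well supported:** Table 2 puts baseline after allocation and the text does not prevent it, so participants may know their arm at baseline. This rests on the column alignment, which looks intact, and on participants learning their arm at or soon after allocation, which the article does not state.
- **Ambiguity only:** section 3 can be read as giving the assessor custody of allocations and treatment records, and needs clarifying.

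Sample size and error rates are unaffected. The amount of bias cannot be estimated from the article. The changes should be made; the baseline order is the one that alters what the trial does and not only how it is described.

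**What to change.** - **Section 2.1:** replace double-blind with open-label, with blinded assessor and statistician.
- **Table 2 and site practice:** have baseline questionnaires completed before allocation, and move the first demographic and economic marks to 0W, ahead of the allocation row.
- **Section 3:** state that allocation codes and treatment records are held by the principal investigator and not by the assessor, in line with the file arrangement in section 2.3.
- **Section 2.3:** state that the person who opens the envelopes is not the assessor.

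The cost is a small change in visit order and file custody, some wording, and a less favourable design label. Recruitment was due to start on 1 July 2025, so any change after that would go through the notification route in section 3. For participants already enrolled, the report should say whether baseline came before or after allocation.
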